### Participant timeline

Both intervention and control treatments will terminate at the completion of the surgery. Subsequent treatments will be the same for both groups according to usual clinical practice.

The following clinical and radiological endpoints will be the focus of the larger randomized controlled trial, but will also be measured on all patients during this pilot trial:*Clinical*: (a) Neurological status (NIHSS) at days 2 and 30 after surgery [23]. (b) Mortality status at 30 days after surgery and every 3 months thereafter until last follow-up after surgery. (c) Disability (mRS) and quality of life (EQ-5D) at 6 and 12 months after surgery [24].*Radiological*: GAD-enhanced brain MRI will be obtained within 72 h after surgery (“first post-operative MR”) and at regular intervals according to each institution’s established practice. This is typically performed every 3 months, or sooner if clinically indicated. Additional post-operative MRIs will be conducted according to each institution’s protocol and reviewed centrally. Additional MRIs are permitted, as needed. Progression-free survival is defined as the number of days from the date of randomization to the date of earliest disease progression based on the mRANO criteria [24] or to the date of death due to any cause, if progression does not occur.

### Schedule of events

**Table Taba:** 

Evaluation	14 days prior to surgery/randomization (screening/enrollment)	Day 0: surgery day (randomization)	Days 1–3: post-OP 1^**st**^ assessment	Day 30 (± 5 days) 2^**nd**^ assessment	6 months (± 2 weeks) post-surgery 3^**rd**^ assessment Collect outcomes	12 months (± 1 month) post-surgery	24 months: annually after (until death, completion of the pilot phase, or lost to F/U)
*Eligibility criteria, medical history, demographics*	X						
*Neurological exam (NIHSS)*	X		X	X			
*MR scan*	X^1^			X ^1^	X^1^	X^1^	X^1^
*Concomitant meds (steroid/antiepileptic)*	X			X	X		
*Received randomly assigned treatment*		X					
*Pathology report*				X			
*Surgical report*				X			
*Adverse surgical* adjuvant tx** events*			X*	X*	X**	X**	X**
*Outcome assessment (clinical secondary outcomes) (EQD-5-mRS)*					X	X	X
*Death*				X	X	X	X
*Progression free survival*				X	X	X	X
*Timing of RTX*				X	X	X	X
*Timing of chemotherapy*				X	X	X	X

*These adverse events only relate to surgery

**These adverse events only relate to adjuvant radiation and/or chemotherapy

^1^These images are obtained through routine clinical practice

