### Data collection and management

#### Plans for assessment, collection of outcomes, and data management

The study case report form (CRF) is the primary data collection instrument for the study. Study personnel, including data entry team members, will use source documents to complete case report forms (CRFs). The information outlined in the schedule of events will be documented in the CRFs.

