### Interim analyses

To enhance monitoring of safety in the supra-marginal resection group, we plan to submit safety reports every 6 months to the DSMB including 30-day mortality data and all serious adverse events (both expected and unexpected) for their review. The DSMB will have formal annual meetings unless they decide to have them earlier based on the submitted safety reports. The initial DSMB meeting will occur either following accrual of the first 10 participants or 6 months after initiation of the study, whichever comes first.

This study will be stopped prior to its completion if (1) the intervention is associated with adverse events that call into question the safety of the intervention, (2) difficulty in study recruitment or retention will significantly impact the ability to evaluate the study endpoints, (3) any new information becomes available during the trial that necessitates stopping the trial, or (4) other situations occur that might warrant stopping the trial.

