### Adverse event reporting and harms

Adverse event information will be entered into the CRF in a timely manner and no later than 15 days from the time the investigator becomes aware of the event. Information about any unexpected serious adverse events that are attributed to the study intervention will be entered into the CRF in a timely manner/within 72 h from the time the investigator becomes aware of the event.

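### The schedule of events limits adverse event collection by attributed cause and time window, at odds with the protocol's own reporting rules, leaving late non-serious surgical events and otherwise-attributed events without a scheduled collection point

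*Protocol article*

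**What the plan says.** The Schedule of events in the protocol article has one adverse event row, marked at five post-operative columns.

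- **Days 1–3 and day 30 (± 5 days):** one asterisk, explained as "These adverse events only relate to surgery".
- **6, 12 and 24 months:** two asterisks, explained as "These adverse events only relate to adjuvant radiation and/or chemotherapy".

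The section on assessment, collection of outcomes and data management ties the case report form to this table: "The information outlined in the schedule of events will be documented in the CRFs".

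Two other sections are broader. Interim analyses promises six-monthly DSMB reports "including 30-day mortality data and all serious adverse events (both expected and unexpected) for their review". Adverse event reporting and harms gives a general entry rule: "Adverse event information will be entered into the CRF in a timely manner and no later than 15 days" from the investigator's becoming aware. Neither limits collection by cause or by time since surgery. The one attribution limit in that last section is on the 72-hour rule, which covers "any unexpected serious adverse events that are attributed to the study intervention".

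**The concern.** The arms differ in the extent of resection. Participant timeline says that later treatment is the same in both. Events caused by surgery are thus the class most directly tied to the randomized difference, and the schedule stops asking for them after the day-30 visit.

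The restriction also makes attribution a gate. Relatedness is normally a field completed for an event already on the form. Here it decides whether the event is entered at that visit at all. Surgeons are not blinded (Who will be blinded). Concealment mechanism concedes that allocation cannot be hidden from the research team at sites where that team randomizes. If such staff make the attribution, recording could differ by arm, and an event never entered cannot be re-adjudicated.

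Two later uses depend on these data. Under Adherence to protocol, the absence of DSMB safety concerns that cannot be rectified is one of two criteria for moving to phase III. The same section plans to carry pilot patients' data into the phase III trial if the protocol does not change in a major way, so a gap in ascertainment would carry over too.

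**Working it through.** The protocol gives no figure to reproduce. The check sets the sections side by side, with one piece of arithmetic.

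**Step 1. Scheduled collection by attributed cause** (Schedule of events, five post-operative adverse event columns)

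| Attributed cause | Days 1–3 | Day 30 | 6 mo | 12 mo | 24 mo | Columns |
|---|---|---|---|---|---|---|
| Surgery | yes | yes | no | no | no | 2 of 5 |
| Radiation/chemotherapy | no | no | yes | yes | yes | 3 of 5 |
| Neither | no | no | no | no | no | 0 of 5 |

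**Step 2. Time without scheduled surgical collection in the first year**

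Formula: (365 − day of last surgical adverse event visit) / 365.

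- Visit on day 30: (365 − 30)/365 = 335/365 = 92%.
- Visit on day 35, end of window: (365 − 35)/365 = 330/365 = 90%.
- Visit on day 25, start of window: (365 − 25)/365 = 340/365 = 93%.

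This is a share of calendar time. It is not a share of events, because surgical risk is not uniform over the year.

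**Step 3. The schedule against the other sections**

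| Event | Schedule of events | Interim analyses | Adverse event reporting and harms |
|---|---|---|---|
| Serious, surgical, after day 30 | no cell | goes to DSMB | entered on awareness |
| Non-serious, surgical, after day 30 | no cell | not covered | entered on awareness |
| Serious, neither cause, any time | no cell | goes to DSMB | entered on awareness |
| Non-serious, neither cause, any time | no cell | not covered | entered on awareness |

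In every row the schedule disagrees with at least one other section. A site that builds its form from the schedule and a site that works from the other two sections would record different events.

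**Step 4. Measures that do not depend on attribution**

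- Mortality: at 30 days, then every 3 months (Participant timeline).
- mRS and EQ-5D: at 6 and 12 months (Participant timeline), and also marked in the 24-month column of the schedule.
- NIHSS: ends at day 30 ± 5 (Secondary outcomes; Schedule of events).

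Death and global function are therefore followed late regardless of cause. The neurological examination is not.

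**The case against.** A reader might infer that late surgical harm is not captured at all, or that the trial stops recording it after day 30. The documents do not support that. The general entry rule and the DSMB reporting rule carry no limit by cause or time. The mRS and EQ-5D are named safety outcomes, are measured late and need no attribution. Neuropsychological testing is to be attempted where feasible, and adjuvant dose, discontinuation and toxicity are tracked. A lasting deficit, which the Introduction names as the main worry, would tend to show in these measures.

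Nor do they support saying that the form excludes serious events from the DSMB report by rule. The form is not shown. The data management section says that it will contain what the schedule lists, not that it will contain nothing else. The schedule may only set what is prompted at visits, with the reporting section governing entry on awareness.

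Biased attribution is likewise possible but not shown. No section says who attributes events, and the protocol uses surgical documentation templates that omit allocation. Focusing on surgical events early and adjuvant toxicity later is also an understandable economy in a 72-patient pilot, and Secondary outcomes treats the first 30 days as the likeliest period for deaths related to surgical adverse events.

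Most of this stands, and it narrows the point. It does not remove it. A deadline running from awareness does not prompt anyone to ask about late surgical events. The DSMB rule covers serious events only. The mRS and EQ-5D cannot identify an event, and the retention section expects them to be the outcomes most vulnerable to loss to follow-up. Secondary outcomes promises change from preoperative baseline on these scales, yet the schedule marks no baseline for either. Finally, the restriction is a stated rule with the word only in both footnotes, so it cannot be put down to detail left to a fuller document.

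**Conclusion.** The point holds as an internal inconsistency with a limited gap in ascertainment. The schedule restricts adverse events by cause and window, while two other sections do not. Surgical events after day 30 (± 5 days) have no scheduled collection point for about 92% of the first year (90–93% over the visit window). Events attributed to neither cause have none at any of the five post-operative visits.

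Because serious events, deaths and global function are covered elsewhere, what is exposed is mainly late non-serious surgical events and events screened out by attribution. How many would be lost, and whether the loss would differ by arm, cannot be computed from the document.

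This rests on two assumptions: that sites follow the footnotes as written when completing visit forms, and that the staff who attribute events may know the allocation. If the form already collects events of any cause at each visit, only the table wording needs correcting.

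**What to change.** Reconcile the Schedule of events with Interim analyses and with Adverse event reporting and harms, so that one rule states which events are recorded and for how long.

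1. Delete the two footnotes that restrict the row by cause.
2. At every existing post-operative visit record adverse events, at minimum all serious events and all surgery-related events.
3. Make relatedness (surgery, adjuvant therapy, other) a separate field completed after the event is entered, so that it describes the event and does not decide its entry.
4. Tabulate adverse events by arm, overall and by attribution.

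The cost is a change to the table and form wording and modestly more data entry at visits already scheduled. No visit is added.

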**Table Tabb:** 

***Radiation therapy***			
***Time***	***6 months***	***12 months***	***24 months***
***Received > 90% of planned dose***			
***Early discontinuation < 50%***			
***Disease progression***			
***Toxicity***			
***Others***

**Table Tabc:** 

***Chemotherapy (temozolomide) therapy***			
***Time***	***6 months***	***12 months***	***24 months***
***Received > 90% of planned dose***			
***Early discontinuation < 50%***			
***Disease progression***			
***Toxicity***			
***Others***			

### Safety criteria

During this pilot study, several safety precautions are being implemented:i)A clearly defined definition of “surgically safe” anatomical criteria.ii)Confirming anatomical suitability by a second designated neurosurgeon centrally.iii)A central adjudication committee, comprising two qualified neurosurgeons, will confirm the suitability of all enrolled cases on an annual basis.iv)Establishing appropriate surgical expertise and volumes for participating surgeons (Additional file 2),v)Mandating minimum intraoperative use of 3D neuronavigation and neurophysiologic monitoring to guide resections for all patients.vi)Incorporating multiple interim safety analyses by the Data and Safety Monitoring Board (DSMB).

### Procedures common to both groups

Imaging, concurrent non-experimental medications, and any adjuvant post-operative care, i.e., external beam radiation therapy plus concomitant and adjuvant temozolomide) including timing, will be according to the standard of care and be recorded. All surgeries will be performed by designated surgeons at each center meeting certain pre-defined surgical skill qualifications (Additional file 2). All surgeries will be performed with the help of intraoperative 3D neuronavigation tools and neurophysiologic monitoring defined by the continuous assessment of the functional integrity of the neural pathway. Other intraoperative adjuncts (e.g., fluorescence-guided, intraoperative MR) are allowed but not required (Additional file 3). The surgical technique (not the extent) for tumor removal is similar in both arms, minimizing any learning curve effect during the trial. Post-operative imaging follow-up with contrast-enhanced brain MRI will be conducted as per institutional practices at regular intervals.

### Sample size

The sample size is based on six sites enrolling patients in this pilot study. All six proposed pilot trial sites are academic tertiary care centers with at least 20–30 malignant glioma surgeries per year (assuming 5 per 100,000/year incidence of new HGG) out of which about one-third are eligible, and assuming that 70% will consent in the 2 years of active recruitment, we will be able to enroll between 45–105 patients. Based on our observational phase I trial (Additional file 4), we were able to enroll at least 1 patient per 2 months, and therefore, a sample size of 72 patients (36 per group) should be feasible for this pilot RCT. If at the end of the study period we recruit 72 patients, we will be 95% confident that these sites will be able to recruit over the same time interval between 56 and 91 patients.

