#### Adherence to protocol

We will define successful adherence as follows:i)Documenting every scheduled clinical assessment on day 2, day 30, 6 months, and 1 year (if alive) in at least 90% of patients.ii)*Implementation of the study protocol* by measuring in at least 90% of enrolled patients the planned primary outcome measure for the larger trial (i.e., overall survival). This rate is comparable to the ability to obtain an outcome in previous large glioma studies [9]

Any reasons for non-adherence to the protocol will be recorded to improve the future larger trial. We will also capture the amount of personnel time required to screen for, consent, enroll patients, complete study procedures, and data collection for the first 5 patients at each site. A strategy to refine the final protocol for the full-scale trial based on the results of the each of above steps will be planned.

The decision to progress to the larger phase III RCT will be based on (1) reaching the primary feasibility target of recruiting at least an average of 1 patient per 2 months per year in each of 6 centers during 2 years of active study participation at each center and (2) no safety or ethical concerns are raised by the Data and Safety Monitoring Board (DSMB) that cannot be rectified. For the future trial, we plan to use overall survival difference (i.e., hazard ratio) to determine the relative efficacy of the interventions and will use data from the pilot study to estimate the required sample size. A meta-analysis assessing 6-month PFS has favored GTR over subtotal resection (STR) (relative risk (RR) 0.72) [7]. For a supra-marginal resection to have a meaningful impact on the survival of HGG patients, a similar improvement of 0.7 hazard ratio would be desired. We calculated that a total of 295 patients (247 deaths) would be required for the trial to have 80% power to detect a hazard ratio of 0.7 (base median overall survival of 14 months) at a two-sided alpha 5% level and planned average length of follow-up of 2 years. Based on our plan to recruit 10 Canadian sites for the phase III study, with an average annual enrollment rate per site of 6 subjects with 2 active surgeons, we anticipate meeting the full enrollment target within 5.5 years. Assuming that there are no major changes to the pilot protocol, we will include the patients’ data in this future larger RCT.

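### The enrolment range of 45–105 does not follow from the stated inputs, which give about 56–84, and 56 to 91 is a confidence interval for expected recruitment worded as a forecast

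*Protocol article*

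**What the plan says.** All the figures stand in one paragraph, the Sample size section of the protocol article.

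- Sites: "The sample size is based on six sites enrolling patients in this pilot study".
- Volume: the sites are "academic tertiary care centers with at least 20–30 malignant glioma surgeries per year".
- Eligibility: "out of which about one-third are eligible".
- Consent, duration and result: "assuming that 70% will consent in the 2 years of active recruitment, we will be able to enroll between 45–105 patients".
- Target: in the observational phase I trial "we were able to enroll at least 1 patient per 2 months", from which the section concludes that "a sample size of 72 patients (36 per group) should be feasible for this pilot RCT".
- Forecast: if 72 are recruited, "we will be 95% confident that these sites will be able to recruit over the same time interval between 56 and 91 patients". No method is named, and the sentence does not mention a mean, a rate or an expected number.

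The Adherence to protocol section makes recruitment one of two conditions for going on to phase III: "recruiting at least an average of 1 patient per 2 months per year in each of 6 centers during 2 years" of active participation. The other condition concerns safety or ethical concerns raised by the data and safety monitoring board.

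**The concern.** The paragraph prints both a set of inputs and a result, so a reader can multiply them, and the product is not the printed range. The printed range is wider at both ends, and its upper end suggests much more room above 72 than the inputs give.

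The closing sentence raises a separate question. It is conditional on having observed 72 and speaks of what the same sites can recruit over the same length of time. Read plainly, that is a statement about a future count. Such a count varies around the true rate, and the rate itself is known only from the first count. An interval that allows for only one of these two sources is too narrow.

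Recruitment is the primary feasibility outcome of this pilot, so these are the figures a funder or site would use to judge whether the target is realistic and how well the pilot predicts later accrual at these centres.

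**Working it through.** **Part 1: the enrolment range**

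Inputs, all from the Sample size section: 6 sites; 20 to 30 surgeries per site per year; 2 years; 1/3 eligible; 70% consent. The incidence of 5 per 100,000 also appears there, but no catchment population is given, so it cannot enter the product.

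Enrolment = sites × surgeries per site-year × years × share eligible × share consenting.

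- Low end: 6 × 20 × 2 × 1/3 × 0.7 = 56 (printed: 45)
- High end: 6 × 30 × 2 × 1/3 × 0.7 = 84 (printed: 105)

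No single changed input repairs this. The number of sites, the years, the eligible share and the consent rate each multiply both ends by the same factor, so the ratio of high to low stays at 30/20 = 1.5. The printed ratio is 105/45 = 2.33. Reading 20–30 as the total over all sites does not help: 20 × 2 × 1/3 × 0.7 = 9.3 and 30 × 2 × 1/3 × 0.7 = 14.

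Working backwards with the other inputs held, each surgery per site-year contributes 6 × 2 × 1/3 × 0.7 = 2.8 patients:

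- 45 / 2.8 = 16.1 surgeries per site-year, below the stated minimum
- 105 / 2.8 = 37.5 surgeries per site-year, not stated

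**Part 2: the interval 56 to 91**

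Take 72 as a Poisson count over the 2 years. The exact 95% confidence limits for its expected value are

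- lower: ½ × χ²(0.025; 2 × 72 = 144 df) = 56.3
- upper: ½ × χ²(0.975; 2 × 73 = 146 df) = 90.7

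These round to 56 and 91, so the plan's figure is reproduced, as an interval for the expected count.

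For a second count Y over an equal period at the same underlying rate:

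- Normal approximation: the difference between the counts has variance 72 + 72 = 144, so 72 ± 1.96 × √144 = 72 ± 23.5, or 48.5 to 95.5.
- Exact conditional method: given the total of the two counts, each is binomial with probability ½. The values of Y not rejected at 2.5% in either tail run from 50 to 98.
- Negative-binomial predictive distribution: 50–97 or 51–98, depending on the prior.

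Coverage of the confidence interval when used as a forecast: simulation at a true mean of 72 gives 84.6%. The predictive probability that Y lies in 56–91 after observing 72 is 86.5%. Both are well short of 95%.

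**Part 3: the target**

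Reading the phase I rate as per site, as the progression criterion does: 6 sites × 0.5 per month × 24 months = 72. This lies inside 56–84. Headroom above 72 is 84 − 72 = 12 at the stated volumes, against 105 − 72 = 33 as printed.

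**The case against.** The best defence of the range is that the inputs are loose. The volume is a minimum and the eligible share is approximate, so 84 is not a strict ceiling and busier sites could bring the total to 105. That stands as far as it goes: a reader might infer that the upper end is overstated by 105 − 84 = 21 patients, but the document does not support calling that an overstatement. What can be shown is that 105 is not derivable from what is printed. The defence does nothing for the low end, because a minimum of 20 cannot produce 45, although there the error is on the cautious side. Unstated inputs can be found that fit, such as 150 eligible patients with consent between 30% and 70%, but the document gives neither figure and nothing shows that they were used.

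On 56 to 91, the limits are arithmetically correct, and the wording can be read as capacity, that is, the underlying rate, for which a confidence interval is right. If the true expected count were known to be 72, a future count would fall in 56–91 about 96% of the time. But the sentence conditions on having observed 72, which leaves the rate uncertain, and it does not say that it means the expected number.

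It is also fair to object that no sample size, analysis or threshold depends on either figure. That stands.

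**Conclusion.** Both sentences are wrong or mislabelled as written. The stated inputs give about 56–84, not 45–105. The figure 56–91 is a confidence interval for expected 2-year recruitment; the matching 95% prediction interval for a further 2-year count is about 50–98, and the printed limits would hold about 85% of such counts. The second part assumes Poisson recruitment at a constant rate common to both periods. Variation between sites would widen the forecast further.

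The consequence is limited, and three stronger inferences are not supported.

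- A reader might infer that 72 loses its justification. It does not: the section derives 72 from the phase I rate, and 72 lies within 56–84.
- A reader might take the middle of 56–84, which is 70, as the expected total and conclude that the trial will probably miss its target. The document states no midpoint, and volumes given as minimums do not define one. Nor does a pooled chance of reaching 72 give the chance of meeting the progression criterion, which is worded per centre and has a second, safety-related condition.
- A reader might infer that the phase III accrual plan is affected. That projection uses 10 sites at 6 patients per site-year, not 56–91.

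What remains is that the apparent room above the target is smaller than printed, and that the pilot forecasts recruitment at these sites less precisely than the closing sentence says.

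**What to change.** Two sentences in the Sample size section.

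1. Replace 45–105 by about 56–84 at the stated volumes. If 45–105 is intended, state the site volumes, eligible share and consent rates that produce each end.
2. Reword the last sentence along these lines: if 72 patients are recruited, the 95% confidence interval for expected 2-year recruitment at these sites is 56 to 91, and the 95% prediction interval for the number recruited in a further 2 years is about 50 to 98, assuming a constant Poisson rate and before allowing for variation between sites.

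The target of 72 and the progression criterion stay as they are. There is no cost in patients, analyses or conduct; the stated headroom becomes somewhat less favourable.
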